#### Data analysis

The analysis will be done using the IBM SPSS statistical software package (IBM Corp., Armonk, New York, USA). Primary analyses of the entire sample will be done according to intention-to-treat principles. A dose-response analysis will be performed to determine effective adherence. Per-protocol analyses will be performed for those participants with at least 70% adherence (corresponding to two trainings per week), as a preliminary estimate of the effective number of training occasions. This is in order to eliminate cross-over and drop-out effects in the total sample, as well as to evaluate the training for those that have reached a pre-defined level of adherence deemed acceptable to have an effect. Sensitivity analyses will be performed to determine whether within-cluster correlations indicate potential effects due to being clustered, for example, by the clinic or by PT. Patient cross-over (i.e., patients changing clinics) is a low-risk possibility and will be recorded in case of occurrence. All outcome variables will be examined for normality using appropriate testing (e.g., Kolmogorov-Smirnov). Complete-case analyses are the primary analyses, and sensitivity analyses will be done depending on the number of missing values. Missing values are not expected to be extensive, and if less than 5% of data is missing, the whole data set will be analyzed along with a sensitivity analysis with appropriate imputed values. If between 5 and 40% of data is missing, appropriate multiple imputation methods will be used, which will be informed by blindly assessing results of the interim analysis, and a complete-case analysis will be done with appropriate sensitivity analyses. If over 40% is missing, a complete case analysis will be done with no sensitivity analysis.

Results will be analyzed using independent samples *t* tests to examine between-group differences of the change from baseline to a 12-week follow-up. Where appropriate, equivalent non-parametric Wilcoxon signed-rank testing will be used to compare between-group differences. The main analysis will focus on the two main outcomes, with secondary outcomes acting as support for these. Secondary outcomes therefore carry less weight and issues with potential error due to the number of evaluations will be discussed when results are presented.

Due to the low range and number of items of the perceived stress scale, Patient Enablement Instrument, and Tegner Activity Scale, as well as the fact that both groups are expected to improve, chi-squared tests will be used to compare within-subjects between-groups means. Rehabilitation motivation and outcome satisfaction will be presented as raw data due to the low number of items. Attrition analyses will also be performed.

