### Procedure

All knee injuries from the PTs patient pool are reported to the SC during weekly contact, in which the SC reminds PTs of inclusion criteria and actively seeks information on knee-injured participants in order to approach all potential participants in the patient pool. The number of patients approached and invited (i.e., eligible, ineligible, and declined participation) will be recorded. The SC contacts potential participants that have consented to a pre-screening interview, during which information is provided, inclusion, and exclusion criteria are verified, and, if eligible, the participant is invited to take part in the study. Information provided to potential participants includes only that there is a “mental training intervention” with no details which could be used to replicate the intervention, adhering to Swedish ethical guidelines for participant informed consent. Following pre-screening, the SC has regular contact with participants and physical therapists in order to receive updates on patient progression through rehabilitation. This ensures proper inclusion timing and reduces the risk of late inclusion by reducing dependency on physical therapists with regard to inclusion criteria, as well as ensuring that eligible participants are included in the trial. Rehabilitation during this period is provided according to rehabilitation protocols prescribed at the discretion of the PT until the participant is able to complete single-leg hop tasks, ensuring proper inclusion timing. When the hop ability criterion is confirmed by the PT, written information is provided, and baseline testing takes place, during which the test leader collects informed consent (Additional File 3 – Informed Consent Materials). The intervention then begins, implementing either CaU or MOTIFS training in the clinical setting during treatment. The intervention period is 12 weeks, as studies have shown that physical [28] and psychological [29] factors can be improved in this time span. MOTIFS training accounts for approximately 20 min [30] in a typical 60-min training session. At least 3 supervised or at-home training sessions are performed per week, whereof at least 6 are supervised by a participating PT during the intervention period, resulting in an intervention dose of 36 possible training sessions, with intensity prescribed by the PT. Participants and PTs are made aware of the possibility to end their involvement in the study. Participants may remove themselves at their discretion, or worsening symptoms may require the PT to change treatment strategy. To ensure that participants complete self-report questionnaires, telephone contact may be initiated.

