##### Adherence

Adherence is measured using a weekly self-report survey regarding the number of completed supervised and at-home rehabilitation sessions, the approximate duration of at-home training sessions, and the approximate duration of MOTIFS training during at-home training sessions (final question answered only by the MOTIFS group). Physical therapist attendance records may be requested to confirm the number of completed supervised rehabilitation sessions over the intervention period. Adherence will be compared between groups to determine whether one treatment has higher adherence rates.

One unvalidated self-report question will be posed to participants in the MOTIFS condition in the adherence survey to assess whether they engaged in imagery during the execution of their rehabilitation exercises. The question was adapted from the Vividness of Movement Imagery Questionnaire [48]: “While doing my rehabilitation exercises, the sport-/physical activity-specific image that I create is:” with responses on a 5-point Likert scale ranging from 1 (“as vivid as though I were actually doing it”) to 5 (“not at all vivid”), with an additional option of not applicable if they did not perform imagery during their exercises. This adherence question also provides an indication of whether the physical therapists were prescribing MOTIFS training during physical rehabilitation sessions.

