### Adverse events/harms

Adverse events are recorded using weekly self-report questionnaires consisting of five questions, distributed using REDCap software. Three questions are directed towards training-related adverse events: “has your knee given way (that is, in the same way as when you injured your knee) in connection with rehabilitation training with your physical therapist or on your own?”; “has your knee swelled up in connection with doing your rehabilitation training with your physical therapist or on your own?”; “have you experienced more pain in your knee in connection with your rehabilitation training with your physical therapist or on your own?” Two questions are related to adverse events in general (i.e., non-training related or overall): “have you had a new knee injury (that made it so you had to use crutches or undergo another surgery in your knee)?”; “have you had any other sickness (influenza, cold, etc.) or injury (sprained ankle, back pain) that resulted in not being able to do your rehabilitation training with your physical therapist or on your own?” Giving way episodes and new injuries which require further medical care are considered serious.

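### The planned dose-response analysis cannot identify an effective number of sessions, because sessions completed are not randomised and may share causes with the 12-week outcomes

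*Protocol article*

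**What the plan says.** The Data analysis section sets the purpose of the analysis in one sentence: "A dose-response analysis will be performed to determine effective adherence". The next sentence adds a threshold analysis: "Per-protocol analyses will be performed for those participants with at least 70% adherence (corresponding to two trainings per week". The article describes that cut-off both as a provisional figure for how many sessions are effective and as a level fixed in advance. Neither analysis is primary: "Primary analyses of the entire sample will be done according to intention-to-treat principles".

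The Procedure section gives the maximum dose, "resulting in an intervention dose of 36 possible training sessions, with intensity prescribed by the PT". The Adherence section says how dose is observed: "Adherence is measured using a weekly self-report survey regarding the number of completed supervised and at-home rehabilitation sessions". Therapist attendance records may be requested to confirm the supervised sessions.

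The Adverse events/harms section lists five weekly questions. Three concern giving way, swelling and increased pain in connection with training. A fourth asks, "have you had a new knee injury (that made it so you had to use crutches or undergo another surgery in your knee". The fifth asks about other sickness or injury "that resulted in not being able to do your rehabilitation training with your physical therapist or on your own". The article does not connect any of these reports to the dose-response analysis.

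The section on adaptive design modification criteria already reads adherence causally. It expects more adherence to bring better outcomes and uses this to accept higher enjoyment as a ground for continuing the trial.

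**The concern.** Asking how many sessions are effective is asking what would happen to the same person at a different number of sessions. The trial randomises clinics to MOTIFS or care-as-usual and does not randomise anyone to a number of sessions. A participant whose knee swells, gives way or is injured again may train less and may also hop less and feel less ready at 12 weeks. A participant who recovers quickly may train less because there is less need. The first pattern makes training look more effective than it is, and the second makes it look less effective. A plain relation between sessions and outcome cannot separate either pattern from a true effect of dose.

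At stake is an adherence threshold, reported as a finding, that reflects who was able or willing to train. It could then appear to confirm the 70% cut-off, or the causal premise behind the enjoyment criterion.

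**Working it through.** **What the documents give.** The maximum dose is 3 sessions × 12 weeks = 36. The planned sample is 106 with an estimated 20% drop-out, so 106 × 0.80 = 84.8, or about 85 analysed. The article gives no figure for this analysis to reproduce, and no knee-event rate.

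**What is assumed.** The true dose effect is zero. Usual sessions have mean 29 and SD s = 5, limited to 0–36. A knee event has probability p (5%, 10% or 20%), costs m sessions (6 or 12) and worsens the outcome by e SD (0.5 or 0.8). The outcome is regressed on sessions with no covariates, two-sided test at 5%, 1,500 simulated trials per setting.

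**Formula.** Ignoring the 0–36 limits, the expected slope per 12 sessions is

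12 × p(1−p)·m·e ÷ [s² + p(1−p)·m²].

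- Mildest setting (5%, 6 sessions, 0.5 SD): p(1−p) = 0.0475; 12 × 0.1425 ÷ (25 + 1.71) = 0.064.
- Strongest setting (20%, 12 sessions, 0.8 SD): p(1−p) = 0.16; 12 × 1.536 ÷ (25 + 23.04) = 0.384.

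**Formula against simulation** (mildest and strongest setting at each event rate). The last column is the mean outcome at or above 70% adherence (0.70 × 36 = 25.2 sessions) minus the mean below it.

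| Event rate | Sessions lost | Outcome loss (SD) | Slope, formula | Slope, simulated | p<0.05 | 70% contrast (SD) |
|---|---|---|---|---|---|---|
| 5% | 6 | 0.5 | 0.064 | 0.076 | 5.9% | 0.063 |
| 5% | 12 | 0.8 | 0.172 | 0.180 | 12.9% | 0.138 |
| 10% | 6 | 0.5 | 0.115 | 0.120 | 7.1% | 0.090 |
| 10% | 12 | 0.8 | 0.273 | 0.297 | 28.5% | 0.259 |
| 20% | 6 | 0.5 | 0.187 | 0.193 | 12.6% | 0.156 |
| 20% | 12 | 0.8 | 0.384 | 0.390 | 50.7% | 0.386 |

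**Both links are needed.** If events do not cost sessions, or do not affect the outcome, the slope is about 0 and the false-positive rate about 5%.

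**The sign can change.** Suppose each SD of a good-recovery trait lowers sessions by a and raises the outcome by b SD. The slope becomes

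12 × [p(1−p)·m·e − a·b] ÷ [s² + p(1−p)·m² + a²],

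which is negative once a·b exceeds p(1−p)·m·e. For a 10% event rate, 12 sessions and 0.8 SD, that limit is 0.09 × 12 × 0.8 = 0.864. With a = 0.5, 1 and 2 and b = a/2, the simulated slopes are +0.23, +0.13 and −0.31. For a = 2 the formula gives 12 × (0.864 − 2) ÷ (25 + 12.96 + 4) = −0.32. With no knee events the simulated slopes are −0.07, −0.25 and −0.89.

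**Effect of adjustment.** With the knee event as a covariate, and no recovery link, the mean slope was −0.01 to +0.02 SD and the false-positive rate 4% to 7%. Removing affected weeks from both sessions done and sessions possible also gave a slope near 0 and about 5%, provided the lost sessions fall in the reported weeks.

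**The case against.** A reader might infer that the protocol says sessions are missed because the knee worsens, and that the analysis will therefore show a dose effect where there is none. The documents do not support either statement.

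- The article gives no reasons or rates for missed sessions. The clause "that resulted in not being able to do your rehabilitation training with your physical therapist or on your own" belongs to the question on other sickness or injury, such as influenza or a sprained ankle. The new-knee-injury question does not mention missed training.
- The remark that "worsening symptoms may require the PT to change treatment strategy" stands among sentences on ending participation. People who leave without 12-week data would not be in a complete-case analysis, so they need not form a group with low dose and poor outcome.
- In the mildest setting the false-positive rate is 5.9% against a nominal 5%. The higher rates need frequent, costly events, and the sign can reverse.

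Four further points stand. The analysis is supportive, and the article ties no decision to it. That it would be used to revise the 70% cut-off is an inference. The slopes above are per 12 sessions, so they should not be set against the effect sizes of 0.1–0.3 in the interim criteria, which are between-arm differences. The article does not say the analysis will be unadjusted, and a model and covariates could properly sit in an analysis plan that is not shown.

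The last point does not remove the concern. The article itself fixes the purpose, and no choice of covariates makes a self-selected, self-reported dose equivalent to an assigned one.

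**Conclusion.** The point holds as one about the inference the article attaches to the analysis. A dose-outcome association in this design cannot determine effective adherence. Knee status is a plausible common cause that the trial itself records, and good recovery is a plausible cause that acts in the other direction.

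Across the settings with knee events alone, the bias is +0.08 to +0.39 SD per 12 sessions, with false positives in 6% to 51% of trials. These figures rest wholly on assumed event rates, sessions lost, outcome losses and an unadjusted linear model. They show what is possible and do not predict the trial's result. Size and direction in the actual data are unknown, and that is sufficient reason not to read a threshold from them. The intention-to-treat comparison of the two main outcomes is unaffected.

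**What to change.** In the Data analysis section:

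1. Describe the dose-response analysis as exploratory and its result as an association. Remove the aim of determining effective adherence.
2. Adjust for arm, the baseline value of the outcome and baseline rehabilitation motivation.
3. Take account of every weekly knee report (giving way, swelling, more pain, new knee injury) and of sickness or injury that prevented training. Do this with covariates, or in a sensitivity analysis that removes affected weeks from both sessions done and sessions possible. The article lists no weekly record of changes in treatment by the therapist, so the adjustment should not rely on one.
4. State that no adherence threshold will be derived from the analysis, and that it will not be used to justify or revise the 70% cut-off.

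Item 4 is needed even after adjustment. Three of the knee questions ask about events in connection with training, so the reports may partly result from dose, and unrecorded reasons for training less remain. The cost is a weaker claim about dose and some extra programming. The data are already collected.

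### The per-protocol set is meant to remove cross-over effects, but its only criterion is a session count that cannot detect cross-over

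*Protocol article*

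**What the plan says.** The Data analysis section makes intention to treat the primary approach and adds a second population: "Per-protocol analyses will be performed for those participants with at least 70% adherence", a level equated with two sessions a week and described "as a preliminary estimate of the effective number of training occasions". Two purposes follow. The first is stated as "This is in order to eliminate cross-over and drop-out effects in the total sample". The second is "to evaluate the training for those that have reached a pre-defined level of adherence deemed acceptable to have an effect". The same paragraph treats cross-over as a patient changing clinic, rates it as low risk and says that it will be recorded. It attaches no consequence for the analysis sets.

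The Adherence section takes adherence from a weekly survey of the "number of completed supervised and at-home rehabilitation sessions", plus session durations. Table 3 lists the same kind of data: number and duration of sessions, and attendance reported by the therapist. The Procedure section sets the dose at 36 sessions over 12 weeks.

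The weekly survey also asks MOTIFS participants how vivid their imagery was, "with an additional option of not applicable if they did not perform imagery during their exercises". The Discussion refers to imagery as a measure of compliance. The per-protocol rule does not use this answer.

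**The concern.** Clinics are the randomised units, so a patient who moves to a clinic of the other arm changes treatment. A criterion that only adds up sessions cannot see this. The text therefore promises that a source of contamination is removed and then applies a rule that leaves it in.

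A related weakness touches the second purpose. By the MOTIFS intervention section, MOTIFS is usual rehabilitation exercise with imagery built in. A MOTIFS participant who reports no imagery throughout has had, in content, usual care, yet can meet the session threshold.

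What is at stake is how the per-protocol result is read. It will be taken as the effect in those who received the assigned training, whereas the rule selects those who did enough rehabilitation of any kind. If it agrees with the intention-to-treat result, that agreement would say little about contamination or imagery use, since neither enters the selection.

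**Working it through.** **Inputs.** 12 weeks and at least 3 sessions per week, supervised or at home (Procedure); 36 possible sessions (Procedure); threshold of at least 70%, glossed as two per week (Data analysis); adherence as a count of supervised and at-home sessions (Adherence, Table 3).

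**The plan's own figures.**
- Dose: 12 × 3 = 36 sessions, as stated.
- 70% of 36 = 25.2, so 26 sessions are needed: 26/36 = 72.2%.
- Two per week: 12 × 2 = 24, and 24/36 = 66.7%. The gloss matches 70% only after rounding. This is a separate matter; the records below qualify under either threshold.

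**Cross-over.** Take a participant who trains three times a week throughout and moves to a clinic of the other arm after week w. Sessions in the assigned arm = 3w; in the other arm = 36 − 3w; total = 36.

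| Move after week | Assigned arm | Other arm | Counted adherence |
|---|---|---|---|
| 1 | 3 | 33 | 36/36 = 100% |
| 3 | 9 | 27 | 100% |
| 6 | 18 | 18 | 100% |
| 9 | 27 | 9 | 100% |

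Every row is in the per-protocol set, including the one with 33 of 36 sessions in the other arm.

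**A more generous reading.** Suppose adherence meant only sessions in the assigned arm. The text does not say so. A participant would then need 3w ≥ 26, so w = 9 (9 × 3 = 27). Moves before that would drop out of the set, but a participant who moved after week 9 would remain, with 9 sessions in the other arm. Cross-over would be reduced, not eliminated.

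**Drop-out.** Someone who stops after week 6 has at most 18/36 = 50% at three sessions a week and is excluded. The count therefore largely does its work for the other effect named.

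**Imagery.** A MOTIFS participant with 26 sessions who marks the imagery question as not applicable in every survey has 26/36 = 72.2% and is included.

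**The case against.** The case for leaving the text alone has four parts.

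- *The analysis plan may complete the definition.* It is not shown, and an article condenses. That would answer a complaint about missing detail. Here, however, the article states both the criterion and the purpose, and the two do not match.
- *The consequence is small.* The primary analysis is by intention to treat, cross-over is rated as low risk, a dose-response analysis is also planned, and the 70% is called preliminary. All of this stands and limits the weight of the point.
- *A session count is a defensible common yardstick.* It applies equally to both arms, whereas the imagery item is unvalidated and asked in one arm only. This also stands. It is a good reason not to put imagery into the main per-protocol rule.
- *Fidelity is supported by other means.* The study coordinator makes three visits to each MOTIFS patient together with the therapist, so a participant who never uses imagery should be unusual. This is fair, but those visits do not feed into the set definition.

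A reader might go further and infer that the set keeps every effect it was meant to remove, including lack of supervision and lack of imagery. The text does not support that. Only cross-over and drop-out are named, and the count deals with most drop-out. Nor does the Procedure section's wording, "whereof at least 6 are supervised by a participating PT during the intervention period", make supervision a condition of per-protocol status. Sessions may be supervised or at home, and nothing in the article treats supervision as the marker of an effective dose.

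**Conclusion.** The point holds for cross-over. The stated rule cannot eliminate cross-over effects, because a participant who switches arms and keeps training can reach 36/36. For imagery the point is one of interpretation: the per-protocol result reflects sufficient rehabilitation sessions rather than confirmed MOTIFS training.

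This rests on reading adherence as the Adherence section and Table 3 define it, and on no exclusion being added in a plan that is not shown.

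A reader might also infer a material loss of power. The documents do not allow that to be calculated. They give neither the expected share of participants who cross over or do no imagery, nor the effect size, standard deviation or intra-cluster correlation behind the 106 participants. The effect is confined to the meaning of a secondary analysis.

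**What to change.** In the Data analysis section, add to the session criterion that participants who changed to a clinic of the other arm during the 12 weeks are excluded from the per-protocol set. The information is already to be recorded, and the condition applies equally to both arms.

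Optionally, add one supportive analysis restricted, in the MOTIFS arm, to participants who reported imagery (an answer other than not applicable) in most of their returned weekly surveys. Label it as selection on behaviour after randomisation in one arm, so that it is not read as a randomised comparison.

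The cost is a sentence or two of text and a slightly smaller per-protocol set. No new data are needed, and the primary analysis does not change. The wording should be settled before unblinded results are seen, so that exclusions are not chosen with the data in view.

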Shifting the focus to individual relevance may influence motor learning and performance of experienced-based movements, according to the OPTIMAL theory of motor learning [21]. This is also supported by the theory of re-investment, which states that motor execution can be disrupted through attempts at conscious control [22]. For example, focusing on how to execute a situation-based (i.e., soccer) task, rather than on movement technique, relies more on automatic processes to create efficient movement [22]. A more external focus also creates an understanding of the applicability of the movement, shifting motivation from extrinsic (outcome-oriented) to intrinsic (inherent satisfaction), which is important for adherence [23]. Adherence may then also influence physical outcomes by virtue of having performed the exercises [24].

Integrating DMI into knee-injury rehabilitation constitutes a potential alternative to improve the effectiveness of rehabilitation by targeting a gap in the rehabilitation literature. This allows for specific interventions that can be used in a clinical environment which aim to address and affect physical, neurological, and psychological aspects.

This study protocol describes an ongoing adaptive randomized controlled trial, the aim of which is to compare the efficacy of rehabilitation with integrated dynamic motor imagery, and rehabilitation alone (care-as-usual) in terms of improving both muscle function and patient-reported outcomes in physically active males and females with a traumatic knee injury and with a goal of returning to physical activity. This approach of integrating physical and psychological aspects in rehabilitation takes a holistic perspective of the injury, in contrast to an isolated physical perspective in care-as-usual rehabilitation.

The main hypothesis is that 12 weeks of rehabilitation with integrated dynamic motor imagery will improve patient-reported psychological readiness to return to physical activity and objective muscle function to a greater extent than CaU rehabilitation.

Secondary aims include examining the effect of rehabilitation with integrated DMI on patient-reported outcomes, performance in a hop battery, and postural orientation. The exploratory aims include a phenomenological interview with patients to gain further insight into the perceived experiences throughout the rehabilitation process.

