#### Adaptive design modification criteria

The mean scores of the main outcomes (side hop and ACL-RSI) will be compared in exploratory interim analyses once *n*=25 participants have been included in both groups. Analyses will be performed by a blinded third-party data management committee (DMC) and blinded to treatment arms until after an initial data analysis and interpretation. The purpose of the interim analysis is primarily to gain data with which a more reliable sample size can be calculated based on observed differences, as well as to identify potential benefits and harms which may thereby determine whether modifications are required. Therefore, differences in the main outcomes from baseline to 12 weeks will be compared using estimations from the previously defined clinically relevant differences as modification criteria, as both groups are expected to improve. Continuation without modification will be allowed if the between-groups difference in ACL-RSI is ≥5 points, and/or muscle function (LSI) in the side-hop test is ≥8 in favor of the MOTIFS group, each analyzed separately. These estimates correspond to a small to medium effect size (Cohen’s *d*≈0.1–0.3) based on previously defined clinically relevant values and will be used to determine the potential for the MOTIFS model to exhibit an effect. However, as previous studies which provide enough data for reliable calculation are lacking, these effect sizes are theoretical estimations which require further data to confirm. The estimates take into account the small sample size in the interim analysis and serve as a guide to whether the differences exhibit a trend indicating acceptable power upon completion of data collection, without unnecessarily prematurely ending the trial. If these initial criteria are not met, difference in enjoyment (PACES) scores of approximately 5 points will be deemed acceptable, estimated based on studies examining the effect of enjoyment on physical activity adherence in uninjured people [53]. Increased adherence to rehabilitation training will likely lead to improved rehabilitation outcomes based on a dose-response relationship, so increased enjoyment is considered an acceptable criterion for the continuation of the trial. Upon completing the interim analysis, the DMC will determine whether these criteria are met, and/or whether modifications are necessary, and a new sample size calculation will be performed.

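### The per-protocol comparison selects on adherence after allocation, so it does not eliminate drop-out effects and is open to selection bias of unknown direction

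*Protocol article*

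**What the plan says.** All of the following is in the protocol article.

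- **Primary analysis (Data analysis):** "Primary analyses of the entire sample will be done according to intention-to-treat principles".
- **Restriction (Data analysis):** "Per-protocol analyses will be performed for those participants with at least 70% adherence (corresponding to two trainings per week". One rule serves both arms.
- **Stated purpose (Data analysis):** "This is in order to eliminate cross-over and drop-out effects in the total sample", and also to "evaluate the training for those that have reached a pre-defined level of adherence deemed acceptable to have an effect".
- **Method (Data analysis):** the between-group test named for change from baseline to 12 weeks is an independent-samples t test, or a non-parametric alternative. No adjustment for predictors of adherence is mentioned.
- **Related analysis (Data analysis):** "A dose-response analysis will be performed to determine effective adherence". Attrition analyses are also planned.
- **Measurement (Adherence):** adherence comes from a weekly self-report survey of completed sessions and is itself an outcome: "Adherence will be compared between groups to determine whether one treatment has higher adherence rates".
- **Rationale (Background):** an external focus is credited with "shifting motivation from extrinsic (outcome-oriented) to intrinsic (inherent satisfaction), which is important for adherence".
- **Rationale (Adaptive design modification criteria):** greater enjoyment can justify continuing the trial because "Increased adherence to rehabilitation training will likely lead to improved rehabilitation outcomes based on a dose-response relationship".

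**The concern.** Allocation makes the two arms comparable as whole groups. Adherence is observed only once treatment is under way, so the subset that reaches 70% is formed by whatever drives adherence in each arm. If those drivers differ between arms and are related to outcome, the two subsets differ for reasons other than the effect of training.

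This is a practical risk here because the protocol's causal account runs through motivation, enjoyment and adherence. The arms also differ in contact: MOTIFS participants have three face-to-face support visits, while Care-as-Usual participants have three telephone calls.

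The stated purpose fails for the same reason. Leaving out people who stopped training conditions on drop-out and does not remove its effect. Nor does a count of sessions remove cross-over, since someone who changes clinic can still log enough sessions.

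At stake is the reading of the secondary result. A gap between the per-protocol and intention-to-treat estimates could be taken as information about training in adherent patients when it may reflect selection alone.

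**Working it through.** **The plan's own figure.** Full dose is 3 sessions × 12 weeks = 36. Two sessions a week give 24/36 = 66.7%, whereas 70% of 36 is 25.2 sessions, or 2.1 a week. The two wordings agree only after rounding to the nearest 10% and need to be reconciled. That is a separate matter: the argument below applies wherever the cut-off lies.

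**Inputs.** The protocol gives no expected share reaching the cut-off, no correlation between adherence and outcome, and no direction. The following are assumptions:
- adherence propensity is normal, and a participant enters the per-protocol set when it exceeds a threshold;
- the outcome change has SD 1 within each arm;
- r is the correlation between adherence and outcome that treatment does not cause;
- p is the share of an arm reaching the cut-off.

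**Formula.** The mean of a standard normal variable in its top fraction p is m(p) = φ(z)/p, with z the normal quantile of p. This gives m(0.5) = 0.798, m(0.6) = 0.644, m(0.7) = 0.497 and m(0.8) = 0.350.

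Per-protocol difference minus intention-to-treat difference = r(MOTIFS) × m(p MOTIFS) − r(CaU) × m(p CaU).

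**Same r in both arms, MOTIFS raises adherence:**

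| CaU / MOTIFS reaching cut-off | r = 0.3 | r = 0.5 | r = −0.3 |
|---|---|---|---|
| 60% / 70% | 0.3 × (0.497 − 0.644) = −0.04 | −0.07 | +0.04 |
| 60% / 80% | 0.3 × (0.350 − 0.644) = −0.09 | −0.15 | +0.09 |
| 50% / 80% | 0.3 × (0.350 − 0.798) = −0.13 | −0.22 | +0.13 |

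Negative values are against MOTIFS. With r = 0 there is no bias. With equal r and equal shares there is also none.

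**Adherence tied more closely to response under MOTIFS** (r = 0.4 against 0.1 under CaU, for example because non-responders to MOTIFS stop), with no true effect:
- 60% / 60%: 0.4 × 0.644 − 0.1 × 0.644 = +0.19
- 60% / 70%: 0.4 × 0.497 − 0.1 × 0.644 = +0.13
- 60% / 80%: 0.4 × 0.350 − 0.1 × 0.644 = +0.08

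**MOTIFS lowers adherence** (CaU 70%, MOTIFS 60%, r = 0.3): 0.3 × (0.644 − 0.497) = +0.04.

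A simulation with 2 million participants per arm reproduced the equal-r figures to within simulation error. They were the same with no treatment effect and with a direct effect of 0.3 SD.

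**The case against.** The strongest reply is that the analysis is secondary. Intention-to-treat is primary, no success criterion rests on the per-protocol result, and the cut-off is described as preliminary. Adherence will be compared between arms and attrition examined, so a reader would see an imbalance. Adjustment in a secondary population is often left to an analysis plan.

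Much of this stands, and it limits the consequence. It does not answer the point, because the article does more than leave a detail open: it fixes a restriction and claims that the restriction achieves something it cannot. The dose-response analysis relates the same post-allocation variable to outcome, and the attrition analyses do not make the adherent subsets comparable.

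It can also be said that leaving out the part of an effect that acts through adherence is not in itself bias, since it answers a different question. That is fair, and the figures above do not rely on it.

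A reader might infer three stronger things that the documents do not support:
- **That the bias most likely runs against MOTIFS.** This needs higher adherence under MOTIFS and a positive correlation that is similar in both arms. Other plausible assumptions reverse the sign.
- **That the protocol predicts higher adherence under MOTIFS.** The Background and the continuation criteria imply it, but the Adherence section treats it as an open question.
- **That the bias can match the effect the trial is sized to detect.** The d of about 0.1 to 0.3 in the protocol describes interim continuation thresholds, which it calls theoretical. It is not the powered effect.

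**Conclusion.** The point holds as a flaw in a secondary analysis. The per-protocol sets are selected on a variable that arises after allocation and that the protocol's own rationale says treatment may affect. The comparison is therefore not of randomised groups, and the claim to eliminate cross-over and drop-out effects is wrong.

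The direction of the bias is unknown. It is about 0.04 to 0.22 SD against MOTIFS if MOTIFS raises the share reaching the cut-off by 10 to 30 points and r is 0.3 to 0.5 in both arms. It is about 0.04 to 0.19 SD in favour of MOTIFS if the correlation is negative, if adherence is tied more closely to response under MOTIFS, or if MOTIFS lowers adherence. The larger values against MOTIFS need gaps of 20 to 30 points; at 10 points the bias is 0.04 to 0.07 SD. Every input is assumed.

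The primary intention-to-treat conclusion is untouched. What changes is how much the per-protocol result can be said to show.

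**What to change.** - Remove the statement that the restriction eliminates cross-over and drop-out effects.
- Adjust the per-protocol comparison for a short, prespecified set of baseline predictors already collected, such as the baseline value of the outcome and one motivation item. Either covariate adjustment or a parsimonious inverse-probability weight would serve.
- Report the share reaching the cut-off in each arm beside the result.
- Label the analysis supportive, and state that a difference from intention-to-treat is not by itself evidence about the effect of completing the training.

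The list must be short. With 106 participants at 1:1 there are 53 per arm, and if 80% of MOTIFS participants reached the cut-off, only about 0.2 × 53 ≈ 11 would miss it. Arm-specific weights built on a dozen or so baseline terms would be unstable.

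The cost is a few lines of text and modest programming. The downsides are a somewhat wider interval and reliance on measured predictors of adherence; selection on unmeasured ones would remain.
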